# Surufatinib combined with transarterial embolization versus surufatinib monotherapy in patients with liver metastatic neuroendocrine tumors: Study protocol for a prospective, randomized, controlled trial

**DOI:** 10.1002/cam4.7131

**Published:** 2024-04-17

**Keywords:** neuroendocrine tumors with liver metastasis, randomized controlled trial, surufatinib, transarterial embolization

## Abstract

**Background:**

More than half of neuroendocrine tumor (NET) patients will experience liver metastasis, and interventional therapy represented by transarterial embolization (TAE) is the main local treatment method. Surufatinib is recommended as a standard systemic treatment for advanced NETs. The efficacy and safety of surufatinib combined with TAE in the treatment of liver metastasis are undetermined. This study was conducted to compare the clinical outcome of surufatinib combined with TAE versus surufatinib monotherapy in liver metastatic NETs.

**Methods:**

This is a prospective, multicenter, open‐label, and randomized controlled trial. Patients diagnosed with liver metastatic NETs will be enrolled. Participants are randomly assigned in a 1:1 ratio to either the experimental group or the control group. Patients will be treated with surufatinib plus TAE in the experimental group, while patients in the control group will receive surufatinib monotherapy. The primary endpoint is progression‐free survival (PFS) assessed by a blinded independent image review committee (BIIRC). The secondary endpoints are investigator‐assessed PFS, liver‐specific objective response rate (ORR), objective response rate (ORR), disease control rate (DCR), overall survival (OS), and incidence of adverse events.

**Discussion:**

This is the first prospective study to investigate the efficacy of surufatinib combined with TAE. We expect this trial to propose a new and effective treatment strategy for liver metastatic NETs.

## BACKGROUND

1

Neuroendocrine tumors (NETs) are heterogeneous neoplasms arising in peptidergic neurons and neuroendocrine cells and generally originate in the gastroenteropancreatic (GEP) tract and the lung. In recent decades, the incidence of NETs has significantly increased.^1^, ^2^

The World Health Organization proposed a classification that distinguishes between well‐differentiated NETs and poorly differentiated NECs (NECs) according to different degrees of pathologic differentiation. G1, G2, and G3 grading levels were classified according to the Ki‐67 index (≤2%, 3%–20%, and >20%) and mitotic rates based on the WHO 2010 classifications in gastroenteropancreatic NETs. Although, compared to most neoplasms, NETs have a better prognosis, more than 20% of patients commonly have distant metastases at diagnosis. Previous research has shown that NETs show a relative preference toward the liver irrespective of the primary site, and approximately 82% of all NET patients have liver metastases in the course of disease.^3^, ^4^ Several treatment options exist, including systemic therapy (such as targeted drugs, somatostatin analogues, peptide receptor radionuclide therapy, and chemotherapy) and local therapy (liver resection, transarterial chemoembolization,^5^ and selective internal radiotherapy). Despite such diverse treatment options, there is still uncertainty about the optimal treatment plan. Prospective clinical trials in NETs with liver metastasis have important clinical significance for improving patient prognosis.

Surufatinib, a novel oral tyrosine kinase inhibitor that selectively targets VEGFR 1, 2, and 3, FGFR1, and so on, is being developed for the treatment of NETs. In 2020, two phase III clinical trials (SANET‐p and SANET‐ep) suggested that the median progression‐free survival (PFS) of the surufatinib group was significantly longer than that of the placebo group (pancreatic NETs: 10.9 months vs. 3.7 months, *p* = 0.0011; extrapancreatic NETs: 9.2 months vs. 3.8 months, *p* < 0.0001).^6^, ^7^ 84% of the enrolled patients had liver metastasis, and 66% of the patients had previously received antitumor treatment in the study. The most common treatment‐related adverse events were hypertension, diarrhea, proteinuria, and liver dysfunction. Thus, surufatinib was recommended as standard systemic treatment for locally advanced and metastatic NETs in China.^8^ Based on that NETs hepatic metastases receive most of their blood supply from the hepatic artery, transarterial embolization (TAE) represents a beneficial treatment option for control of symptoms as well as tumor growth,^5^ which is recommended by the guidelines of China and abroad. However, there is no prospective trial to confirm the feasibility of surufatinib plus TAE.^9^, ^10^, ^11^ To investigate this possibility, we planned a prospective study on the efficacy and safety of surufatinib combined with TAE compared to surufatinib monotherapy in patients with liver metastatic NETs, trying to explore a better regimen for NETs with liver metastasis and clinical guidelines.

## METHODS

2

The study is approved by Biomedical Ethics Review Committee of West China Hospital of Sichuan University. The trial is registered at Chinese Clinical Trial Registry (ChiCTR2300071991). The study will be performed at West China Hospital, Sichuan University. Written informed consent will be obtained from all participants. The trial protocol and this manuscript have been developed in line with the Standard Protocol Items: Recommendations for Interventional Trials (SPIRIT) guidelines (Figure 1).^12^

**FIGURE 1 cam47131-fig-0001:**
[figure not shown]
The SPIRIT flow diagram of this trial. NETs, neuroendocrine tumors; TAE, transarterial embolization; RECIST, Response Evaluation Criteria in Solid Tumors; transarterial embolization; PD, progression disease; PFS, progression‐free survival; ORR, objective response rate; DCR, disease control rate; OS, overall survival.

### Trial design

2.1

This is a prospective, open‐label, and randomized controlled trial. Patients who have been diagnosed with liver metastatic NETs (G1, G2) will be enrolled. Participants are randomly assigned in a 1:1 ratio to either the experimental group or the control group. Patients will be treated with surufatinib plus TAE in the experimental group, while patients in the control group will receive surufatinib monotherapy. This study will prospectively collect progression‐free survival (PFS), liver‐specific objective response rate (ORR), objective response rate (ORR), disease control rate (DCR), overall survival (OS), incidence of adverse reactions, and quality of life (QOL). Unless the patients experience PD or intolerable toxicity, each case should be treated for at least 8 weeks before efficacy evaluation.

## TREATMENT

3

### Experimental group

3.1

Patients will receive 300 mg of surufatinib orally once a day, combined with TAE. The first TAE treatment should be performed within 14 days after starting surufatinib. During TAE, there is no need to stop surufatinib, and the frequency and interval of TAE should be determined by the interventional physician or multidisciplinary treatment. In the experimental group, patients should receive TAE at least once; for patients with a liver tumor burden exceeding 50%, it is recommended to perform TAE in stages to reduce complications. Each subject will receive treatment until disease progression, intolerable toxicity, or informed consent withdrawal (Figure 2).

**FIGURE 2 cam47131-fig-0002:**
[figure not shown]
Overview of phases of the trial. ECOG PS, Eastern Cooperative Oncology Group performance status; TAE, transarterial embolization; ORR, objective response rate; DCR, disease control rate; OS, overall survival.

### Control group

3.2

Patients will receive 300 mg of surufatinib orally once a day. Each subject will receive treatment until the PD, intolerable toxicity, or informed consent withdrawal (Figure 2).

## ENDPOINTS

4

### The primary endpoint

4.1

The PFS was assessed by a blinded independent image review committee (BIIRC).

### The secondary endpoints

4.2

Investigator‐assessed PFS, liver‐specific objective response rate (ORR), ORR, disease control rate (DCR), overall survival (OS), and incidence of adverse events.

## INCLUSION AND EXCLUSION CRITERIA

5

### Inclusion criteria

5.1

Histologically or cytologically confirmed G1/G2 NETs with liver metastasis; the location of primary lesions and whether surgical resection is performed are not limited;Aged 18–75 years old;Life expectancy of longer than 3 months;Eastern Cooperative Oncology Group performance status score (ECOG) ≤2;According to imaging and surgical evaluation, the liver lesion is unresectable or the patient is unable to tolerate surgery, and the primary lesion has no serious complications (perforation, obstruction or hemorrhea that cannot be managed by medical therapy);The liver must have at least one measurable objective tumor lesion according to the RECIST version 1.1 standard, with a maximum diameter of ≥1 cm for spiral CT examination and ≥2 cm for conventional CT or MRI, and it should be conducted within 28 days before enrollment.Adequate organ functions as follows:

Absolute neutrophil count ≥1500/mm^3^, leukocyte≥3000/mm^3^, platelet count ≥75,000/mm^3^, hemoglobin ≥9.0 g/dL; total bilirubin≤1.5 × upper limit of normal (UNL); serum creatinine ≤1.5 × UNL; alanine aminotransferase, aspartate aminotransferase ≤5 × UNL;
8Participate the study voluntarily and sign the informed consent document.

### Exclusion criteria

5.2

Histologically or cytologically confirmed neuroendocrine carcinoma, small cell carcinoma, and goblet cell carcinoid;Functional neuroendocrine tumors that require long‐acting somatostatin analogues (SSAs) to control symptoms, such as islet cell tumors, glucagonoma, gastrinoma, vasoactive intestinal polypeptide‐secreting tumors, adrenocorticotropic hormone‐secreting tumors, and carcinoid syndrome;Urine protein: ≥2+ or >1.0 g/24 h;Patients with hypertension (> 140 mmHg systolic or >90 mmHg diastolic) that cannot be adequately controlled with antihypertensive agents;Patients with serious gastrointestinal diseases that may affect drug absorption, including but not limited to the presence of a pepticulcer, ulcerative colitis, active gastrointestinal bleeding, gastrointestinal obstruction, and severe diarrhea;Patients with a history of severe hemorrhagic disease (single blood loss >30 mL) within 3 months, hemoptysis (single blood loss >5 mL) within 1 month, or thromboembolic events (including pulmonary embolism and cerebral infarction) within 12 months;Patients received surgical treatment (excluding biopsy) within 4 weeks or the surgical incision healed in poor condition;Patients with severe cardiovascular diseases, including but not limited to acute myocardial infarction, unstable angina, heart failure, ventricular arrhythmias requiring medication, and left ventricular ejection fraction <50%, a corrected QT interval of ≥480 ms on ECG;Patients with other malignant tumors with a disease‐free survival <5 years (except for cured basal cell carcinoma of the skin, cured cervical in situ carcinoma, and cured gastrointestinal tumors through endoscopic mucosal resection);Patients with immune deficiency diseases or HIV infection;Patients with severe uncontrolled acute infection (infection causing fever above 38 centigrade);Patients with active hepatitis B or active hepatitis C, and hepatitis B virus (HBV) DNA ≥ 1 × 10^4^ IU/mL, and hepatitis C virus (HCV) RNA≥1 × 10^3^ IU/mL;Patients with other serious medical and surgical diseases and the investigator believes that it is not suitable to participate in this clinical trial;Patients who participated in clinical trials of other novel drugs within 4 weeks;Pregnant or lactating women or patients with fertility (male or female with less than 1 year of amenorrhea) are unwilling to take contraceptive measures;Patients who have severe study drug allergy and hypersensitivity;Unsuitable for enrollment in the opinion of the investigator.

### Assessment and follow‐up

5.3

The comprehensive information of eligible patients needs to be collected at least 1 week before the start of treatment, which includes: medical history, physical examination, ECOG PS score, the test of clinical chemistry, hematology and coagulation, electrolytes, liver, kidney, and thyroid function, CA 199, CA 125, CEA, NSE, CT or MRI scan, and ECG. Disease evaluation is performed every 12 weeks by CT or MRI based on RECIST version 1.1. Whether CT or MRI is used is up to the investigator, but the evaluation method, machine, and technical parameters should be kept as consistent as possible throughout the entire treatment. The imaging examination window is ±7 days. The disease condition and survival status will be recorded via face‐to‐face visits or by phone every 4 weeks. After the first evaluation, patients with SD, PR, or CR continued treatment, while PD patients were excluded from the study.

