### Sample size and statistical analyses

5.5

Referring to the results of two phase III clinical studies of surufatinib (SANET‐p and SANET‐ep), the sample size calculation was performed using the log rank method on PASS, and the hazard ratio (HR) was set as 0.6 with a β error of 0.2 and a two‐sided α level of 10%. Patients were randomly assigned to the experimental group and control group in a 1:1 ratio, with an estimated dropout rate of 5% for each group. The study will last for 3 years, and the enrollment of subjects will occur in the first 2 years. Therefore, it is estimated that at least 62 patients are needed in the experimental group and 61 patients in the control group. A total of 123 patients and 96 events are needed in both groups.

The primary objectives are to determine BIRC‐assessed PFS. The secondary objectives are to determine investigator‐assessed PFS, OS, ORR, and safety. PFS is defined as the time from the beginning of treatment until the first observed disease progression or cancer‐related death. OS will be evaluated from the start of treatment to the death of patients. In this trial, ORR is defined as CR + PR according to RECIST 1.1. The 95% confidence intervals (CI) of the ORR will be calculated. The Kaplan–Meier method and a two‐tailed log rank test are used to evaluate PFS and OS.

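### The follow-up rule takes patients with progression at the first evaluation out of the study, although overall survival runs to death and progression elsewhere ends treatment only

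*Protocol article*

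**What the plan says.** All references are to the protocol article.

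- **Section 5.3 (Assessment and follow-up), the rule once the first evaluation is done:** "patients with SD, PR, or CR continued treatment, while PD patients were excluded from the study".
- **Section 5.3, schedule:** "Disease evaluation is performed every 12 weeks by CT or MRI based on RECIST version 1.1", and "The disease condition and survival status will be recorded via face‐to‐face visits or by phone every 4 weeks". No end is given for the 4-weekly contact.
- **Section 2.1 (Trial design):** "This is a prospective, open‐label, and randomized controlled trial". It also asks that, barring progression or intolerable toxicity, "each case should be treated for at least 8 weeks before efficacy evaluation".
- **Sections 3.1 and 3.2 (treatment groups):** progression is one of the reasons to end treatment. Neither section says that it ends study participation.
- **Sections 4.1 and 4.2 (endpoints):** the primary endpoint is PFS by a blinded independent image review committee (BIIRC). Investigator-assessed PFS and OS are separate secondary endpoints.
- **Section 5.5 (Sample size and statistical analyses):** "OS will be evaluated from the start of treatment to the death of patients". A first observed progression is a PFS event. The design is a hazard ratio of 0.6, power 80%, two-sided alpha 10%, 96 events and 123 patients (62 experimental, 61 control).

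**The concern.** Ending treatment and leaving the study are different things. OS needs every randomised patient followed to death or study end, whatever happens at the first scan. A rule that takes early progressors out of the study stops that follow-up in a prognostically selected group. If the combination works as the design assumes, that group is larger in the control arm, so the loss is informative and unequal. Survival data not collected after exit may be impossible to recover later.

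There is a smaller second consequence. Blinded review and the investigator can disagree. If a local progression call takes a patient out and the BIIRC does not confirm it, later scans are missing and the patient is likely to be censored for the primary endpoint at a moment of suspected progression.

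**Working it through.** **1. The plan's own event number.** Schoenfeld's formula with 1:1 allocation:

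events = 4 × (1.645 + 0.842)² / (ln 0.6)² = 94.8, rounded up to 95. The plan states 96.

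Power at 96 events = Φ(√96 / 2 × 0.5108 − 1.645) = Φ(0.858) = 80.4%. The stated 96 is reproduced to within one event.

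**2. Progression by the first scan.** Inputs: exponential PFS (assumption); control median 9.2 to 10.9 months (assumption, taken from the two surufatinib arms cited in the Background); experimental median = control / 0.6; first scan at 12 weeks = 2.76 months.

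Proportion progressing = 1 − 0.5^(2.76 / median).

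| Control median | Control | Experimental | Total |
|---|---|---|---|
| 9.2 months | 18.8% × 61 = 11.45 | 11.7% × 62 = 7.3 | 18.7 |
| 10.9 months | 16.1% × 61 = 9.8 | 10.0% × 62 = 6.2 | 16.0 |

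The loss is about 1.6 to 1 from control. If the first evaluation came at 8 weeks, the shares would be 11.0% to 12.9% and 6.8% to 8.0%, or about 11 to 13 patients in all.

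**3. Effect on OS.** Simulation with a true OS hazard ratio of 1.00, OS median 24 or 36 months, PFS–OS correlation 0.3, 0.5 or 0.7 through a Gaussian copula, PFS hazard ratio 0.6, 24 months of uniform accrual and cut-off at month 36. The OS medians and correlations are assumptions. Patients who die before the scan are not counted as removed, so the removed shares are somewhat below those in step 2.

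- All patients followed: hazard ratio 0.99 to 1.01, which is simulation noise around 1.00.
- Early progressors censored at progression: 1.03 to 1.12.
- Early progressors dropped from the OS analysis: 1.02 to 1.11.

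A ratio above 1 is unfavourable to the experimental arm, so the bias favours control.

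**4. Effect on PFS by blinded review.** A progression that the BIIRC confirms is already an event and loses nothing. Only discordant first-scan calls matter. With an assumed 10% to 30% discordance:

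- 0.10 × 16.0 = 1.6 patients; 96 − 1.6 = 94.4 events; power 80%.
- 0.30 × 18.7 = 5.6 patients; 96 − 5.6 = 90.4 events; power 78%.

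This counts each discordant patient as a lost event. It measures lost information, not the bias from informative censoring.

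**5. Worst case.** If first-scan progressors were also deleted from the PFS analysis:

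- 96 − 18.7 = 77.3 events; power 72.6%.
- 96 − 16.0 = 80.0 events; power 73.9%.

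**The case against.** The strongest reply is that the sentence contrasts patients who go on with treatment with those who do not, so it may mean only that patients with progression come off study treatment. The line on survival contact has no stop at progression, and OS is defined to death. The text is a condensed article, and post-progression follow-up is often left to the full protocol. This supports a benign intention, and no passage sets out to stop OS follow-up. It does not remove the conflict: the words say that these patients leave the study, the treatment rule is already given elsewhere, and no passage keeps them in follow-up.

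Three stronger readings are tempting and go beyond the documents.

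- **First-scan progressors are deleted from the primary analysis.** Section 5.5 makes a first progression a PFS event and removes no one. The power of about 73% to 74% in step 5 is therefore a worst case, not the expected result.
- **The loss applies at every scan.** Discordance of 10% to 30% across all 96 events would leave 86 to 67 events and power of 77% to 67%. The sentence speaks of the first evaluation and does not state the same exit for later scans.
- **The investigator's call triggers the exit.** No passage says whose call it is. It is a fair inference from the open-label design and the separate investigator-assessed endpoint, and the blinded-review part of this point depends on it. The censoring of discordant patients is likewise presumed, since no censoring rule is shown.

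It is also fair to say that the OS bias is modest, concerns a secondary endpoint and works against the experimental arm.

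**Conclusion.** The point holds as a conflict in the stated follow-up rule. Section 5.3 removes patients with progression at the first evaluation from the study, against its own survival contact, the treatment sections and the OS definition.

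Applied as written, it would end OS follow-up for about 16 to 19 early progressors, about 1.6 times as many from control as from the experimental arm, and would shift a null OS hazard ratio to about 1.03 to 1.12 if they are censored. The imbalance follows from the design hazard ratio. Its size rests on exponential PFS and the assumed control median, and the size of the OS shift also on the assumed OS medians and correlations.

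The threat to the primary endpoint is limited to about 2 to 6 discordant patients at the first scan, with power at about 78% to 80%, and only if the triggering call is the investigator's. The documents do not support a claim that the primary analysis is seriously underpowered because of this sentence. Correction is still warranted: lost survival data may not be recoverable, and the remedy is cheap.

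**What to change.** Reconcile Section 5.3 with Sections 3.1, 3.2 and 5.5. Replace the exclusion wording with a statement that patients with progression:

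- end study treatment as Sections 3.1 and 3.2 already state;
- count as PFS events and stay in all analyses;
- continue the existing 4-weekly survival contact until death or study end.

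Add that, where the BIIRC has not confirmed progression, the scheduled 12-weekly imaging continues until BIIRC progression, new anticancer therapy or withdrawal. State whose assessment of progression is meant.

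This changes follow-up and data collection only; no dose or treatment rule is altered. The sample size figures do not change: 96 events and power of 80.4% under the plan's own inputs. The cost is a wording amendment, continued contacts on a schedule that already exists, and a few extra scans in discordant cases.

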### Dosage adjustments

5.4

Toxic reactions should be classified based on NCI‐CTC AE version 5.0. Dosage adjustments of surufatinib should be guided by toxicity grading criteria. General principles include:
For adverse reactions, appropriate treatment should be administered to alleviate patient symptoms and signs. This may involve administering anti‐hypertensive drugs for hypertension and hepatoprotective drugs for liver function abnormalities.Pre‐existing adverse events at baseline, if deemed necessary by the researcher, will be adjusted according to changes in toxicity grading.In cases of multiple simultaneous adverse reactions, the most conservative dose adjustment plan should be implemented.Following adverse reactions, surufatinib dosage should not be re‐increased, and dosage should not be reduced more than three times during each patient's treatment course.The maximum duration of medication suspension due to toxic reactions is 4 weeks. If the adverse reaction decreases to ≤1 level within this period, dosage adjustment to resume medication is recommended. Specific dosage adjustment principles are outlined in the drug instructions. The principles of dosage adjustment are presented in Table 1.If researchers determine that a toxic reaction is unlikely to escalate to a serious or life‐threatening event, such as a rash, patients may continue treatment at the original dose without reduction or interruption. In the case of non‐hemolytic anemia, if better relief can be attained through interventions like blood transfusion, erythropoietin, and iron therapy, dosage reduction or treatment interruption may be unnecessary.

**TABLE 1 cam47131-tbl-0001:** Dose adjustment of surufatinib.

Dose adjustment gradients	
Original dose of surufatinib	300 mg qd po, q4w
The first reduction	250 mg qd po, q4w
The second reduction	200 mg qd po, q4w
The third reduction	200 mg/250 mg d1‐d21 po, q4w

